#### Analysis of key feasibility outcomes

Descriptive statistics will be employed to summarise key feasibility and acceptability outcomes, including trial recruitment, retention, therapy engagement and treatment fidelity. Participant flow through the trial will be reported in accordance with the Consolidated Standards of Reporting Trials (CONSORT) extension for feasibility and pilot trials,^49^ detailing the number of referrals received per month, recruitment sources, number of participants contacted and assessed for eligibility, numbers consented (with reasons for ineligibility or declining participation when available), randomisation to trial arms, adherence to allocated interventions and retention at the 3- and 6-month follow-up assessments.

All quantitative data analysis will be conducted according to a pre-specified statistical analysis plan prepared by our trial statistician (co-author [name]) and available on request from the corresponding author. Descriptive analyses of therapy session records and fidelity checklists will estimate the adherence of therapists to the intervention protocol. AEs and SAEs will be tabulated by trial arm and reviewed to assess the safety and acceptability of the intervention and study procedures.

In addition, descriptive statistics (mean, SD, minimum, maximum, range and percentage of missing data) will be reported for all outcome measures at baseline and follow-up assessments, disaggregated by trial arm. These data will inform feasibility parameters for a future definitive trial, including estimates of variance and preliminary outcome differences. No hypothesis testing for clinical effectiveness (p values) will be conducted, but where appropriate, mean differences, SD and 80% CIs will be calculated at follow-up time points to provide a preliminary indication of the ‘promise of efficacy’ of the ChUSE intervention on valued trial outcomes.^61^

To support the feasibility of future health economic evaluation, the completeness and quality of data collected using the EQ-5D,^62^ EQ-5D-Y^63^ and CHU-9D^64^ will be summarised. Intervention and TAU service costs will be estimated using national unit cost data from NHS England and the Personal Social Services Research Unit.

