#### Sampling and recruitment targets

As a feasibility trial, a formal power calculation is not required.^49 50^ In line with recommendations for pilot trials, we aim to randomise 60 young people and parent/caregiver dyads.^51 52^ This sample size is considered sufficient to estimate outcome measure variability and inform the design of a future definitive trial. Recruitment will take place over 19 months, with a minimum target of four participants per month in the first year. A recruitment review will be conducted at month 12, with contingency plans to extend to additional NHS trusts if 75% of the target sample has not been achieved 6 months before the end of the trial.

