### Randomisation and blinding

Participants will be randomly allocated on a 1:1 basis to either (1) ChUSE talking therapy plus parent sessions alongside TAU or (2) TAU alone. Randomisation will be conducted independently using a web-based service (sealedenvelope.com), with concealed allocation via a pseudo-random sequence employing random permuted blocks of varying sizes, unknown to the study team.

Following baseline assessment, research workers will notify the chief investigator (CI) or a delegate about participant eligibility for randomisation. The CI or trial therapist (or delegate) will then enter the participant ID into the secure online system, which will immediately generate the allocation. Allocation outcomes will be communicated only to unblinded team members (CI, Co-CI and the trial therapist) and centrally logged on the secure platform and a restricted-access randomisation log.

Blinding will be maintained for research workers and trainees responsible for data collection. Research workers and trainees will not access clinical notes or treatment information post-randomisation and will be routinely reminded, along with participants and clinical teams, to avoid disclosing treatment allocations during assessments. The CI, therapist and co-investigators will remain unblinded in line with standard practice for psychological intervention trials. Any breaches of blinding will be documented, and where possible, follow-up will be reassigned to a blinded researcher.

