### Follow-up assessments and safeguarding procedures

Participants will be invited to complete follow-up assessments at 3 months (T1) and 6 months (T2) post-randomisation. These assessments will replicate the baseline battery of measures, as shown in tables 1 and 3. To enhance active safety monitoring, AEs will be systematically assessed during each contact point and through consultation with clinical notes.

**Table 3 T3:** Measures and completion times

Instrument used in the proposed trial	Number of items	Indicative completion time
Strengths and Difficulties Questionnaire Self-Report version for 11–17-year-olds^69^	25	10–15 min
Manchester Voices Inventory for Children (MAVIC;^23^)	18	10–12 min
Unusual Experiences Questionnaire (MUSEQ;^70^)	9 (only issued at T0)	10–15 min
Stirling Children’s Wellbeing Scale^71^	12	8–10 min
Brief Self-compassion Scale^72^	12	8–10 min
KidCOPE scale^73^	15	10–20 min
EQ-5D-Y^63^	5	5 min
Child Health Utility Instrument (CHU-9D;^64^)	9	5–8 min
Child Stigma Scale (CSS) – adapted multisensory experiences^74^	7	5 min
Treatment as usual checklist (TAU checklist)	12	8–10 min

EQ-5D, EuroQol-5 Dimension questionnaire; EQ-5D-Y, EuroQol 5-Dimensional Questionnaire for Youth; UEQ, Unusual Experiences Questionnaire.

Each assessment is expected to last approximately 1 hour, with options for breaks or multiple shorter sessions to accommodate participants’ needs (see table 3). T2 may take up to 2 hours, as this data point includes qualitative interviews. For all participants, there is then an option to provide further qualitative feedback through a Qualtrics survey, based on the same questions as the semi-structured interview guides. There is one survey for CYP and one for parents/caregivers. On completion of the final follow-up, participants will be formally debriefed about the feasibility of the RCT and, where consent has been provided, reminded about possible future contact for research updates or follow-up studies.

To minimise missing data, the research team will make multiple attempts to contact participants before considering them lost to follow-up. Data collection methods will include in-person, telephone, video conferencing or postal options. Any spurious or incomplete data will be reviewed by the research team, who will determine appropriate actions such as verification or re-collection.

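### A free improvement, not an error: the follow-up mean differences name no adjustment for the baseline score, and the baseline–follow-up correlation is not among the listed statistics

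*Protocol article*

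**What the plan says.** In Analysis of key feasibility outcomes, the article lists the summaries for every outcome measure by arm at baseline and follow-up: mean, spread, extremes and missingness. The comparison between arms is then given in one clause: "where appropriate, mean differences, SD and 80% CIs will be calculated at follow-up time points". It is offered as a preliminary indication only, and "No hypothesis testing for clinical effectiveness (p values) will be conducted". The same section says that "All quantitative data analysis will be conducted according to a pre-specified statistical analysis plan"; that plan is not shown. No baseline covariate, change score, residual SD or baseline–follow-up correlation is named. The word unadjusted does not appear either.

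The baseline data exist. Screening and enrolment places T0 before randomisation. Follow-up assessments and safeguarding procedures says of T1 and T2: "These assessments will replicate the baseline battery of measures". The exception is the unusual experiences questionnaire (UEQ/MUSEQ), which Tables 1 and 3 give at T0 only.

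On size and allocation, "we aim to randomise 60 young people and parent/caregiver dyads" and "a formal power calculation is not required". "Participants will be randomly allocated on a 1:1 basis", using "random permuted blocks of varying sizes, unknown to the study team". No stratification or minimisation on a baseline score is mentioned. Parameters for a later sample size calculation are part of the primary objective (Objectives) and are listed under Primary feasibility outcomes.

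**The concern.** The sentence settles the statistic, the interval level and the time points, so it can be read as a complete description of the estimate: a difference between two follow-up means. In a trial of 60, the arms will often differ at baseline by a noticeable fraction of an SD. A difference that does not use the T0 score carries part of that gap into the reported value. It also gives away precision that the collected data could supply.

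The second issue is planning. If the definitive trial adjusts for baseline, its sample size depends on the residual SD or, equivalently, on the raw SD together with the correlation. The listed statistics provide the raw SD but neither of the other two, although supplying such parameters is a stated primary purpose of the study.

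**Working it through.** **Inputs.** From the article: 60 dyads, 1:1, so 30 per arm. No dropout rate is given, so I use the green retention threshold in Table 4 as a scenario: 0.70 × 60 = 42, or 21 per arm. The 80% interval is taken as two-sided. The correlation r between the T0 score and the follow-up score is not in the article; I assume 0.3 to 0.7 and also show zero. Results are in units of the outcome SD, taken as equal across arms and time points.

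**The plan's own figure.** There is none to reproduce. The 60 rests on recommendations for pilot trials, with no effect size, SD or precision target behind it.

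**Interval width.**

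- Unadjusted half-width = t(0.90, 2n−2) × √(2/n). With n = 21: 1.303 × √(2/21) = 1.303 × 0.3086 = 0.402.
- Baseline-adjusted half-width = t(0.90, 2n−3) × √[(1−r²) × (2/n) × (1 + 1/(2n−4))]. The last factor is the average cost of estimating the slope. With n = 21 and r = 0.5: 1.304 × √(0.75 × 0.09524 × 1.0263) = 1.304 × 0.2708 = 0.353.

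| Estimate | 30 per arm | Ratio to unadjusted | 21 per arm | Ratio to unadjusted |
|---|---|---|---|---|
| Unadjusted | 0.335 | 1 | 0.402 | 1 |
| Adjusted, r = 0 | 0.338 | 1.009 | 0.408 | 1.014 |
| Adjusted, r = 0.3 | 0.322 | 0.963 | 0.389 | 0.967 |
| Adjusted, r = 0.5 | 0.293 | 0.874 | 0.353 | 0.878 |
| Adjusted, r = 0.7 | 0.241 | 0.721 | 0.291 | 0.724 |

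Break-even at 21 per arm is where √(1−r²) = 0.4021/0.4076 = 0.9865, so r = √(1 − 0.9732) ≈ 0.16. Above that, adjustment narrows the interval on average.

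**Chance imbalance.** The baseline difference between arms has SD √(2/n): 0.258 at 30 per arm and 0.309 at 21. The probability that it exceeds 0.3 SD in either direction is 2 × [1 − Φ(0.3/0.258)] ≈ 25% at 30 per arm and 2 × [1 − Φ(0.3/0.309)] ≈ 33% at 21. Given an imbalance d, the unadjusted difference is shifted by r × d on average. For d = 0.3 that is 0.09, 0.15 or 0.21 SD at r = 0.3, 0.5 or 0.7.

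**Validity.** A simulation with no treatment effect (6,000 trials per setting; n = 30 and 21; r = 0.3, 0.5, 0.7) gave an average error within 0.007 SD of zero and coverage of 79.3% to 80.4% for both estimators. The unadjusted estimate correlated with baseline imbalance at 0.30 to 0.70, about r in each setting; the adjusted one did not (at most 0.02 in size).

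**Planning parameter.** Raw variance divided by residual variance is 1/(1−r²): 1/0.91 = 1.10, 1/0.75 = 1.33 and 1/0.51 = 1.96 for r = 0.3, 0.5 and 0.7. Without r, a planner cannot move from one to the other.

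**The case against.** The strongest reply is that the choice of covariates is normally left to the analysis plan, that the article points to one, and that a condensed article should not be faulted for omitting it. This stands to a large extent. A reader might infer that the trial has fixed an unadjusted comparison that ignores the baseline. The text does not support that: it neither says unadjusted nor excludes a model, and a mean difference can be an adjusted one. In the same way, silence on stratification is not a statement that there is none. What remains is that the article chose to name the statistic, the interval level and the time points, and a reader holding only the article would take the difference to be raw.

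A reader might also infer bias or an invalid interval. Neither follows. Chance imbalance is part of the sampling error that the interval already expresses, and baseline summaries by arm will make it visible.

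Nor is the raw SD a wrong parameter. It is a standard input to sample size. Used alone it errs towards a larger trial, and the article does not say that the definitive trial will adjust.

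Finally, little depends on the estimate: there are no hypothesis tests, and none of the five progression domains in Table 4 uses it. That limits the weight of the point. It does not remove it, because sample-size parameters are part of the primary objective.

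**Conclusion.** The point holds as a near-costless improvement and a request for clarity, not as an error. If the sentence is followed literally, the estimate is valid but less precise than the data allow. At 21 per arm, adjustment would narrow the 80% interval by about 3% at r = 0.3, 12% at r = 0.5 and 28% at r = 0.7, and widen it by about 1% at r = 0. It would also remove the dependence of the realised estimate on chance baseline imbalance. The separate gap, that no correlation or residual SD is listed, matters for planning a baseline-adjusted trial whichever estimator is used here.

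These sizes rest on an assumed correlation, on 70% retention spread evenly over the arms, and on a roughly linear relation between baseline and follow-up. The conclusion would fall away if the analysis plan already specifies adjustment and the correlations, leaving only a sentence to add to the article.

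**What to change.** In Analysis of key feasibility outcomes, and in the analysis plan if it is not already there:

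- State that each T1 and T2 difference and its 80% CI comes from a linear model of the follow-up score on arm and the T0 score of the same measure, where one exists. This excludes the UEQ/MUSEQ, which Tables 1 and 3 give at T0 only. Keep the rule of no p values.
- Report, for each measure, the raw SD, the residual SD and the T0–T1 and T0–T2 correlations as the parameters for the definitive trial.
- Give a simple rule for missing T0 scores, since participants may leave questions unanswered.
- If the analysis plan already does this, say so in the article.

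The cost is a few sentences, one estimated slope per model and the missing-score rule. No new data, visits or participants are needed.

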#### Qualitative evaluation

Interviews will be guided by topic guides co-developed with the PPIE groups and refined iteratively throughout the trial. Qualitative inquiry will be undertaken to explore participant and clinician experiences of trial processes and intervention delivery, which is essential for informing the development and future implementation of complex interventions.^65^ Semi-structured interviews will be conducted by members of the research team at mutually convenient locations, either face-to-face, online via Microsoft Teams or by telephone. Young people may be accompanied by a trusted adult if they wish.

Interviews will be audio-recorded, transcribed verbatim using secure transcription software and subsequently reviewed and anonymised by a second member of the research team. Transcripts will be analysed using the Framework Method,^66^ a structured and transparent approach suitable for multidisciplinary health research teams.^67^ Regular interpretation meetings will be held among the qualitative research team and LEAG to promote reflexivity and transparency during the analytic process.

Future access to anonymised final datasets will be considered case-by-case by the CI and TSC, ensuring no risk of participant identification. Study findings will be disseminated through peer-reviewed publications, conference presentations, public forums and participant summaries, in line with NIHR publication requirements.

## Nested MAVIC-R

This nested validation study within the ChUSE Trial aims to assess the reliability, validity and usability of the MAVIC-R. MAVIC-R is a novel communication and assessment tool designed to help young people describe their USEs (which may be comforting, banal or distressing) or DSEs in a non-pathologising, supportive manner. This study seeks to explore the tool’s psychometric properties and explore its practical applications in NHS CAMHS and related services.

### Research questions

How effectively does MAVIC-R facilitate communication about DSEs with young people?Which components are most helpful in exploring personal appraisals and meanings of DSEs?How do young people, caregivers and professionals perceive the tool’s utility?What are the practical and therapeutic implications of its use in CAMHS?

### Research design

#### Phase 1: MAVIC-R refinement

Discussions with the ChUSE PPIE groups will inform updates to the existing MAVIC, expanding its scope from voice-hearing to multisensory experiences. Insights from these consultations will guide revisions to language and content.

#### Phase 2: validation study

A mixed-methods design will assess the psychometric properties and practical acceptability of the MAVIC-R:

**Quantitative**: An online survey with young people will assess item properties and factor structure via exploratory factor analysis (EFA).**Qualitative**: Mental health professionals will trial the tool in practice and provide feedback through interviews on its implementation and acceptability.

### Participant recruitment

Up to 150 young people (aged 8–18) with lived experience of USEs, recruited through professional and lived experience networks, such as voice collective.10 parents/caregivers of young people with USEs.10 multiservice professionals working with young people experiencing USEs.

Inclusion criteria

Young people aged 8–18, fluent in conversational English, with personal experiences of one or more USEs.Caregivers with current or past experience of supporting a young person with USEs.Professionals with regular experience working with young people experiencing USEs.

Exclusion criteria

Young people outside the specified age range or whose current mental health prevents participation.Professionals/caregivers without relevant experience.Autistic young people whose USEs are solely attributed to sensory processing differences.

### Recruitment process

Participants will be recruited via the RRDN, NHS networks, peer organisations (eg, voice collective) and professional contacts. The same referral process as the wider ChUSE trial will be followed, with practitioners completing brief referral forms with consent.

### Consent/assent

Participants will provide electronic consent via Qualtrics for surveys or audio-recorded consent for in-person interviews. For those under 16, caregiver consent and participant assent will be obtained.

### Data collection and analysis

Audio-recorded interviews and focus groups will be transcribed and analysed thematically^68^ using NVivo. Qualitative survey data will also be analysed thematically, and quantitative survey data will be analysed in SPSS. Data will be screened for missingness and item correlations examined and sampling adequacy assessed via KMO and Bartlett’s tests. EFA using maximum likelihood extraction with oblique rotation will determine factor structure, guided by scree plots, Kaiser’s criterion and parallel analysis. Reliability will be tested via Cronbach’s alpha and item-total correlations.

### Expected outcomes and dissemination

If validated, the MAVIC-R will provide a practical, non-stigmatising tool for facilitating discussions about USEs with young people, supporting tailored, person-centred care. Its use could foster more holistic, youth-informed care pathways within CAMHS and other youth services. Findings will be disseminated via peer-reviewed publications, stakeholder summaries and multimedia resources for young people, families and professionals. This study will also enable the inclusion of a validated, youth-specific measure in a future definitive ChUSE trial.

### Trial endpoints, ethical and regulatory considerations and data management

The intervention period for this trial is scheduled to conclude by 1 March 2026, with all data collection for the trial completed by 1 June 2026. The nested validation study will be completed by 1 December 2026. Prior to study commencement, the protocol, consent materials and study documents will obtain favourable NHS Research Ethics Committee (REC) and Health Research Authority (HRA) approvals, with local capacity and capability agreements from participating NHS trusts. The study will adhere to the Declaration of Helsinki, Good Clinical Practice and the UK Policy Framework for Health and Social Care Research (2017).

Regulatory compliance will be maintained through appropriate approvals for all participating sites, timely submission of amendments and regular oversight from the sponsor and TSC. Protocol deviations will be formally logged and corrective actions agreed on collaboratively.

Risk management procedures will include bespoke standard operating procedure (SOPs) for safeguarding, clear limits of confidentiality, procedures for managing participant distress and strict lone working and infection control policies for face-to-face contact.

AEs and SAEs will be monitored closely, recorded according to established SOPs and reviewed for severity, relatedness, expectedness and seriousness. SAEs that are unexpected and related will be reported to the REC and sponsor in line with standard HRA timelines.

Data management will comply with the Data Protection Act 2018 and GDPR. All personal data will be pseudonymised, securely stored and deleted or anonymised at study end. Research data will be stored on encrypted servers with access restricted to authorised study personnel. Final datasets and supporting materials will be archived securely with the Sponsor.

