1.4. Coping Health Inventory for Parents

1.5. EQ-5D

### Trial design

This study will take the form of a feasibility RCT with an embedded process evaluation. It will employ a single-blind, parallel-group design, comprising two arms: (1) a brief psychological intervention involving 4–6 sessions of individual talking therapy for DSEs, with the optional offer of up to three sessions for parents/caregivers, in addition to TAU and (2) TAU alone. Participants in the intervention arm will also be offered a joint session zero with the trial therapist to discuss taking part in the intervention and to plan appointments. Outcome assessments will be conducted with all participants (n=60 parent–child dyads) at baseline (T0), at the end of the intervention (3-month post-randomisation, T1) and at 6-month post-randomisation (T2). At T2, participants will be invited to take part in qualitative interviews to inform the process evaluation. Participants who do not wish to take part in qualitative interviews will be sent a brief online questionnaire via Qualtrics to enable participants to provide feedback on their experience of being in the trial and their experience of the intervention or CAMHS, depending on which arm of the trial they were randomised to. The trial is due to run between October 2024 and November 2026.

While the primary focus of the study is on feasibility outcomes, the process evaluation will generate both quantitative and qualitative data to enhance understanding of potential mechanisms of change, the acceptability of the intervention, preliminary indications of clinical promise within CAMHS settings as well as likely cost drivers and wider system consequences. Quantitative measures will help to track changes in symptoms and well-being over time, while qualitative feedback will capture participants’ experiences of the intervention, trial procedures and how they have experienced their engagement in the trial. Qualitative interviews with practitioners (n=20) will also be conducted to inform interpretation of contextual factors and future implementation considerations.

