#### ChUSE intervention

The feasibility trial will deliver the ChUSE intervention through qualified, NHS-employed, HCPC-registered clinical psychologists trained and supervised in the protocol by the study’s CI. The manualised intervention will comprise ideally seven 50-min sessions (four child-focused and up to three parent coaching sessions) delivered over a 3-month period. While the intervention will always remain brief, there is some flexibility in the number of sessions offered to young people to support engagement for up to a maximum of six sessions. This is to allow for pacing of content and accommodate breaks or shorter sessions as required by families with different needs. There will also be a session zero offered to all participants in the trial arm to attend as a child–parent/caregiver dyad. After each session, the therapist will complete an adherence checklist to monitor progression towards therapy milestones, the use of intervention strategies in line with the manual and any deviations.^56^

Parents/caregivers of children in the intervention arm will be offered the parent sessions alongside the child-focused therapy. Importantly, parental engagement in the parent sessions will not be a prerequisite for children to access individual therapy. The structure and delivery format of both child and parent components were informed by PPIE consultations, which recommended offering a choice of in-person or online sessions via Microsoft Teams to enhance accessibility.

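### The recruitment length, trial dates and data-collection end date disagree by about 5 months, so dyads randomised after 1 December 2025 could not reach T2

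*Protocol article*

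**What the plan says.** All references are to the protocol article.

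- Trial design: "The trial is due to run between October 2024 and November 2026".
- Sampling and recruitment targets: "Recruitment will take place over 19 months, with a minimum target of four participants per month in the first year". The target is set in the same place: "we aim to randomise 60 young people and parent/caregiver dyads".
- ChUSE intervention: the sessions are "delivered over a 3-month period".
- Follow-up assessments and safeguarding procedures: participants are invited to "follow-up assessments at 3 months (T1) and 6 months (T2) post-randomisation".
- Randomisation and blinding: "Participants will be randomly allocated on a 1:1 basis".
- Trial endpoints, ethical and regulatory considerations and data management: the intervention period is "scheduled to conclude by 1 March 2026, with all data collection for the trial completed by 1 June 2026". The nested MAVIC-R study has its own end date, 1 December 2026.
- Progression criteria: recruitment is green at an average of 3 or more dyads per month. Retention is green at 70% or more, counted on end-of-treatment and follow-up assessments. Completion means all four child sessions.

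The article does not give the date on which recruitment opens.

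**The concern.** From the first randomisation to the last T2, the plan needs the recruitment period plus 6 months. The printed dates do not leave that much time. If the sites recruit for 19 months and data collection still stops on 1 June 2026, the last dyads in will have no T2, however acceptable they find the trial. Retention is one of the five progression domains, and it would then partly measure the calendar. If recruitment instead closes early enough for everyone to reach T2, the window is about 14 months and the target of 60 needs faster accrual than the plan states. Two teams reading different sections could each follow the article and run different trials.

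**Working it through.** **Inputs.** Recruitment 19 months; T2 at 6 months; treatment period 3 months; end of intervention 1 March 2026; end of data collection 1 June 2026; target 60 dyads; allocation 1:1. Assumption: recruitment opens on 1 October 2024, the earliest date that fits the trial dates. I read the target of four participants per month as four dyads.

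**Step 1: dates that follow from 19 months.**
- End of recruitment: 1 Oct 2024 + 19 months = 1 May 2026.
- Last treatment period and T1: + 3 months = 1 Aug 2026.
- Last T2: + 6 months = 1 Nov 2026.

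This agrees with the November 2026 trial end. It does not reproduce 1 March or 1 June 2026; both are 5 months too early.

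**Step 2: last usable randomisation under the printed end dates.**
- For T2: 1 June 2026 − 6 months = 1 Dec 2025.
- For a full treatment period: 1 March 2026 − 3 months = 1 Dec 2025.
- From 1 Oct 2024 to 1 Dec 2025 is 14 months, so 19 − 14 = 5 recruitment months fall outside.

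**Step 3: sensitivity to the start date.** Opening on 1 Nov 2024 cuts off 6 months; opening on 1 Jan 2025 cuts off 8. For 19 months to end by 1 Dec 2025, recruitment would have to open on 1 May 2024. That is before the stated trial start, ethics approval (2 May 2024) and registration (14 June 2024).

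**Step 4: dyads without T2, and the resulting ceiling on T2 retention.** The last column applies an illustrative 10% ordinary dropout to the dyads who can reach T2.

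| Accrual pattern | Randomised by month 14 | No T2 by 1 June 2026 | T2 ceiling | After 10% dropout |
|---|---|---|---|---|
| 4/month until 60 (month 15) | 4 × 14 = 56 | 4 (7%) | 56/60 = 93% | 84% |
| 48 in year one, then 12 over 7 months | 48 + 2 × 12/7 = 51.4 | 8.6 (14%) | 51.4/60 = 86% | 77% |
| Even, 60/19 = 3.16/month | 3.16 × 14 = 44.2 | 15.8 (26%) | 14/19 = 74% | 66% |

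Under even accrual, 5% dropout already brings retention to 0.737 × 0.95 = 70%, the edge of green.

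**Step 5: ChUSE arm.** At 1:1, about half of the affected dyads are due treatment: about 2, 4 or 8 in the three rows. For these, a full 3-month period does not fit before 1 March 2026.

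**Step 6: closing recruitment at month 14 instead.** 3 × 14 = 42 dyads; 4 × 14 = 56 dyads; reaching 60 needs 60/14 = 4.3 per month.

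**The case against.** **The printed 2026 dates may be left over from a superseded timetable.** They fit 19 months from 1 May 2024 exactly, so the sponsor may never have meant to cut off follow-up. That is plausible, but the article does not say so. The remedy would be the same correction.

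**Nineteen months may be the slip.** The Progression criteria point the other way. One participant per month is equated there with fewer than 20 in all (1 × 19 = 19), and the green rate gives 3 × 19 = 57, close to 60. Over 14 months the same rates give 14 and 42.

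**November 2026 may cover the nested study.** The shortfall does not rest on that date. Nineteen months plus 6 is 25 months, and October 2024 to 1 June 2026 is 20. The nested study is also dated separately.

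**The effect may be small at the planned pace.** This stands. The recruitment target is front-loaded, and at four per month in the first year only about 4 to 9 dyads lose T2. Retention then stays green after 10% dropout. The month-12 review and the option to add trusts may also support accrual, although neither changes the dates.

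**Treatment may finish sooner than 3 months.** This also stands. Completion is four sessions, and nothing in the article prevents some ChUSE dyads randomised after 1 December 2025 from attending four before 1 March 2026. Only T2 has a fixed interval.

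**Conclusion.** The contradiction holds. Assuming recruitment opened on 1 October 2024, the stated recruitment length and follow-up overrun the printed end dates by 5 months; any later opening makes the gap larger. About 4 to 16 of 60 dyads would have no T2 by 1 June 2026, depending on accrual.

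Four stronger readings are tempting but not supported:

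- A reader might infer that about a quarter of the sample is lost. That needs even accrual at 3.16 per month, or a rate near the green threshold (15 of 57 at 3 per month). The planned first-year minimum gives 7% to 14%. If that minimum counted individuals, so 2 dyads per month, the share would be (60 − 24 − 2 × 36/7)/60 = 43%, but dyads are the natural reading.
- A reader might infer that retention must drop to amber. Of the three patterns examined, only even accrual threatens the 70% threshold.
- A reader might infer that every affected dyad misses treatment. Dyads in the treatment-as-usual arm have no ChUSE course to finish, and some in the ChUSE arm could complete four sessions in time.
- A reader might take the four-week rule under Consent, assent and withdrawal as a T2 visit window. It governs when a withdrawn participant may opt back in.

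The trial tests no hypotheses, so the harm is to the feasibility estimates and to the conduct of the trial.

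**What to change.** State the date recruitment opens, and give one consistent timetable across Trial design, Sampling and recruitment targets, and the section on trial endpoints and data management. Either of two routes resolves it:

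1. Keep 19 months of recruitment and move the two 2026 dates about 5 months later: intervention to about 1 August 2026 and data collection to about 1 November 2026. This stays within the November 2026 trial end only if recruitment opened at the start of October 2024. Opening on 1 November 2024 puts the last T2 at 1 December 2026, and the trial end must then move too.
2. Keep 1 June 2026, set the last randomisation at 1 December 2025, and restate recruitment as about 14 months with the sample size it delivers: 42 dyads at 3 per month or 56 at 4 per month.

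No change to the retention or completion denominators is needed, because under either route every dyad's follow-up fits within the timetable. The cost is a date correction by amendment. The first route extends the intervention and data-collection dates; the second means stating a smaller sample or a higher accrual rate.
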